## Abstract

**Background:**

Over 50% of patients with upper limb paresis resulting from stroke face long-term impaired arm function and ensuing disability in daily life. Unfortunately, the number of effective treatments aimed at improving arm function due to stroke is still low. This study aims to evaluate a new therapy for improving arm function in sub-acute stroke patients based on mental practice theories and functional task-oriented training, and to study the predictors for a positive treatment result. It is hypothesized that a six-week, mental practice-based training program (additional to regular therapy) targeting the specific upper extremity skills important to the individual patient will significantly improve both arm function and daily activity performance, as well as being cost effective.

**Methods/design:**

One hundred and sixty sub-acute stroke patients with upper limb paresis (MRC grade 1–3) will participate in a single-blinded, multi-centre RCT. The experimental group will undertake a six-week, individually tailored therapy regime focused on improving arm function using mental practice. The control group will perform bimanual upper extremity exercises in addition to regular therapy. Total contact time and training intensity will be similar for both groups. Measurements will be taken at therapy onset, after its cessation and during the follow-up period (after 6 and 12 months). Primary outcome measures will assess upper extremity functioning on the ICF level of daily life activity (Wolf Motor Function Test, Frenchay Arm Test, accelerometry), while secondary outcome measures cover the ICF impairment level (Brunnstrom-Fu-Meyer test). Level of societal participation (IPA) and quality of life (EuroQol; SS-Qol) will also be tested. Costs will be based on a cost questionnaire, and statistical analyses on MAN(C)OVA and GEE (generalized estimated equations).

**Discussion:**

The results of this study will provide evidence on the effectiveness of this mental practice-based rehabilitation training, as well as the cost-effectiveness.

**Trial registration:**

Current Controlled Trials [ISRCTN33487341)

## Background

The incidence of stroke in the Netherlands was 2.2/1000 in 2000 [1]. Over 50% of patients with upper limb paresis resulting from stroke face long-term impaired arm function and a ensuing disability in daily life [2]. Although early rehabilitation treatment in the first phase of stroke is currently advised in clinical guidelines, little evidence is available on such treatment for improving arm/hand function in the same period [3]. Recently, constrained induced movement therapy (CIMT), in which the affected arm must be used due to immobilizing the other, appears to have had a positive effect on arm/hand function in sub-acute stroke patients [4]. However, even long after the stroke only small arm function improvements are reported in a select minority of patients, which stands in contrast to the far better recovery of leg function.

Some studies have shown task-oriented treatment to positively affect arm function recovery in stroke patients [5]. More recently, 'movement imagery' has emerged, targeting the cognitive processes associated with enhanced motor performance and specific skilled movements in healthy persons. Regularly applying this technique in training and competition is called 'mental practice'. Sports psychology research has shown that mental practice can optimize athletes' execution of movement and acquisition of new, skilled behaviors [6,7]. Moreover, combining mental practice training principles with active movement training appears more beneficial than mental practice training alone [6].

In neuroscience, interest in movement imagery has grown in line with improvements in brain mapping techniques. Results from brain imaging experiments suggest that executed and imagined movements share a common neural substrate [8-10]. This has led to the hypothesis that mental practice may contribute to the activation of neural loops and movement patterns for which the brain has a kind of motor print [11]. Mental practice might be used alongside physical rehabilitation in patients with neurological disorders and will probably be most effective in the early recovery stage during which the reorganization of brain patterns is most prominent [10].

The possible benefits of movement imagery on motor performance in acute and chronic stroke patients have been investigated in several studies. Page et al., in a small feasibility study using movement imagery in stroke patients, found a marked improvement in their arm function compared to that of the control group [12]. Similar effects in the training of neglect and motor skills have been reported by Smania et al. and Yoo et al. [13,14]. It seems, then, that although the brain is damaged by stroke, the ability to train using mental practice is retained.

The effects of mental practice on small chronic stroke groups have been reported in several studies [14-22] using different mental practice techniques and intensities. In 2006, Braun et al. presented a systematic review focusing on effectiveness of mental practice training in improving upper extremity functioning, but drew no definite conclusions except that further research using clear definitions of mental practice content and standardized outcome measurements are needed [21]. In 2007, based on a randomized controlled trial for chronic stroke patients, Page et al. confirmed the short-term effectiveness of mental practice in improving upper extremity function [23].

Only one article has reported on the long-term effect of mental practice in stroke patients. This was based on an evaluation conducted just one month after training; the conclusions were positive [22]. The effectiveness of mental practice in stroke, however, is likely influenced by factors such as the ability to perform motor imagery, cognitive functioning, gender, handedness, dysphasia, precise lesion location and time elapsed since the stroke [10,24]. Whether these factors are indeed predictive of therapy outcome and whether mental practice is also effective over the long term in sub-acute stroke patients is currently unknown.

Based on the latest body of evidence, it is hypothesized that mental practice applied in a training regime involving arm function tasks will lead to a significant and long-lasting improvement in stroke patients' arm function. Furthermore, since rehabilitation depends upon the learning of new behaviors (this is associated with brain plasticity), the treatment should include much repetition [2], start early after the stroke [2], be personally rewarding to the patients and provide as much experience as possible of various activities.

### Aims

The aim of the proposed research project is to systematically investigate the therapeutic potential of a mental practice-based therapy in the (partial) restoration of arm/hand function in sub-acute stroke patients. This aim has led to the following research questions:

1. Does a six-week, mental practice-based rehabilitation regime for patients with upper extremity paresis in the sub-acute stroke phase improve arm function and daily activity performance as compared to usual care?

2. What are the prognostic factors for a good therapy outcome?

3. Is a regime such as that described in (1) cost effective as compared to usual care?

## Methods/Design

### Study design

A multi-centre, single-blinded, randomized controlled trial will be conducted to evaluate the effects of six weeks of mental practice-based treatment on arm function in unilateral stroke patients. The evaluation will span the full post-stroke year. Assessment will take place upon entry to the study; post-treatment and follow-up assessments will be performed on three moments during the year (see Figure 1 flow diagram). The Study protocol was approved by the Medical Ethical Committee of the Rehabilitation Foundation Limburg. The study will start in March 2008 and will last till September 2010.

**Figure 1 F1:**
[figure not shown]
The design of the study.

### Setting

Patients from rehabilitation departments in the Hoensbroek rehabilitation centre as well as regional hospitals in South Limburg, the Netherlands, will be included. Patients can enter both the intervention and control training groups.

### Study population

Patients who meet the inclusion criteria in Table 1 will be referred by a consultant in rehabilitation medicine. The sample size calculation (two groups and two-sided testing) was performed using data derived from Bonifer et al.'s [25] study in which stroke patients had a mean Wolf Motor Function Score on the functional ability scale of 3.91 with a standard deviation of 1.11. An assumed clinically relevant difference between groups of at least 10%, an alpha of 0.05 and a power (1-β) of 0.85 would necessitate 145 patients. With an estimated follow-up loss of approximately 10%, 160 participants (2 * 80) are thought to be necessary.

**Table 1 T1:** Inclusion criteria

- first stroke
- post-stroke time of 2–6 weeks
- clinically diagnosed central paresis of arm/hand with elbow flexor strength MRC grade 1–3
- age 18–85
- no severely impaired cognition
- no severe neurological, orthopedic, rheumatoid or cardiac impairments prior to stroke
- no severely comprehension-impaired communication

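### The 145 patients from the sample-size calculation is the number per group but is used as the trial total, so 160 patients give about 56% power, not 85%

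*Protocol article*

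**What the plan says.** The calculation is in the Study population section of the protocol article. It is for two groups with two-sided testing and takes from a cited study a "mean Wolf Motor Function Score on the functional ability scale of 3.91 with a standard deviation of 1.11". The target is a between-group difference of at least 10%. With those inputs, "an alpha of 0.05 and a power (1-β) of 0.85 would necessitate 145 patients". After an allowance of about 10% for loss to follow-up, "160 participants (2 * 80) are thought to be necessary".

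The figure of 145 is therefore treated as the number for both groups together. The abstract confirms this, since it gives 160 patients for the whole trial.

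**The concern.** For two groups and a comparison of means, the standard formula returns a number per group, which must be doubled to get the trial total. Here the stated inputs return 145 per group, and the article carries 145 forward as the total. The match is exact, which points strongly to a missed doubling.

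The WMFT is one of the primary outcomes and the only one for which a calculation is given. If the stated power is wrong, the chance of missing a difference that the article itself calls clinically relevant is not 15% but, for the comparison described, 40% to 45%. A non-significant result would then invite more confidence in the absence of an effect than the trial can support.

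**Working it through.** **Inputs, all from the Study population section:** two groups, 1:1; two-sided alpha 0.05 (z = 1.960); power 0.85 (z = 1.036); SD 1.11; mean 3.91; difference 10%; loss about 10%; planned total 160.

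**One reading is needed.** The article does not say what the 10% is a percentage of. The only mean it gives is 3.91, so the difference is taken as 0.10 × 3.91 = 0.391 points.

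**Step 1: reproduce the article's figure.**

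- Standardised difference: 0.391 / 1.11 = 0.352.
- n per group = 2 × (1.960 + 1.036)² × 1.11² / 0.391² = 144.7, so 145.
- The noncentral t calculation gives 146 per group (power 84.8% at 145, 85.1% at 146).
- Total evaluable: 2 × 145 = 290.

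So 145 is reproduced exactly as a per-group number and not at all as a total.

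**Step 2: how 160 was reached.** 145 × 1.1 = 159.5, which rounds to 160. (Dividing by 0.9, the usual way to allow for 10% loss, gives 161.1, hence 162; this is a minor point.) For the stated inputs, 290 / 0.9 = 322.2, so 323 enrolled, or 324 for equal groups.

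**Step 3: power of the planned size.** Two-sided t-test, difference 0.391, SD 1.11:

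| Evaluable per group | Basis | Power |
|---|---|---|
| 72 | 160 less 10% | 55.5% |
| 72.5 | 145 in total | 55.8% |
| 80 | all 160 analysed | 60.0% |
| 145 | 290 in total | 84.8% |

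The normal approximation gives 56.1% at 72 and 60.6% at 80 per group.

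**Step 4: what 85% power corresponds to.** With 72 per group the detectable difference is 0.558 points, and 0.558 / 3.91 = 14.3%.

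**Step 5: other readings of the inputs.**

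| Reading | n per group (total) | Power at 72 / 80 per group |
|---|---|---|
| Two-sided, 0.5 points (10% of the scale maximum of 5) | 89 (178) | 77% / 81% |
| Two-sided, 0.4 points (0.391 rounded) | 139 (278) | 57% / 62% |
| One-sided, 0.391 points | 116 (232) | 68% / 72% |

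No two-sided reading that was tried gives 145 in total. A one-sided test with 0.5 points comes near it (142), but it contradicts the stated two-sided test and does not use the cited mean.

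**Step 6: effect of baseline adjustment.** In an ANCOVA at one visit, the residual SD is 1.11 × √(1 − r²), where r is the correlation between baseline and outcome. The article gives no r, so these values are assumptions. With 72 per group, power is 68% at r = 0.5, 75% at r = 0.6 and 84% at r = 0.7. It reaches 85% at r = 0.714.

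**The case against.** The strongest reply is that the trial will not be analysed by an unadjusted t-test at one visit. The Effect evaluation section plans MAN(C)OVA and GEE, and Table 2 schedules the WMFT at baseline and three later visits. Suppose the correlation between all visits is equal, the effect is a constant 0.391 points, and the analysis is a baseline-adjusted mean of the three later visits. With 72 per group, power would then be about 88% at a correlation of 0.33, 90% at 0.5 and 96% at 0.7. This stands as a limit on the harm: under favourable assumptions the planned analyses could exceed 85%. But without baseline adjustment the same averaging gives 73% at a correlation of 0.5, and a single-visit ANCOVA gives the lower figures in Step 6. The sample-size paragraph claims no gain from either source and states no correlation, so its 85% cannot rest on one.

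Two further points are fair. First, the base of the 10% is a reading; the alternative of 0.5 points raises power to 77% to 81%, still below 85%. Second, the Effect evaluation section carries the last observation forward for missing T2 or T4 data and replaces participants who lose T0 or T1 data. The number analysed may therefore approach 160, and 60% may be the better figure than 56%. Neither point restores the stated power.

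**Conclusion.** The concern holds. By the article's own inputs, 145 is the number per group, and the total required is 290 evaluable patients. For the two-sided, two-group comparison it describes, 160 enrolled patients give 55.5% power after 10% loss and 60.0% with no loss, against the 85% stated.

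This rests on reading the 10% as 10% of 3.91, which the exact match with 145 supports, and on an unadjusted comparison, which is all that the calculation describes. Power under an adjusted or repeated-measures analysis may be considerably higher, but it depends on correlations that the article does not give.

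**What to change.** Rewrite the sample-size paragraph so that it:

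- states that 145 is the number per group for the stated inputs, 290 evaluable in total;
- gives the power of the trial as planned: with 160 enrolled and 144 evaluable, about 56% for a 0.39-point difference in an unadjusted comparison (60% if all 160 are analysed), or 85% for about 0.56 points (14%);
- expresses the target difference in absolute points on the WMFT functional ability scale, so that the base of the 10% is no longer open;
- names the powered analysis. A baseline-adjusted ANCOVA is the simplest choice, since the WMFT is measured at T0 and MAN(C)OVA is already planned. State the assumed correlation beside its power: 68% at 0.5, 84% at 0.7, 85% at about 0.71. If the repeated-measures GEE is to carry the power claim instead, state its assumptions in the same way.

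The cost is wording and a less favourable stated power. It needs no extra patients or procedures. Keeping 85% power for 0.391 points without adjustment would instead mean enrolling about 323 patients (324 for equal groups).

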### Recruitment and randomization

Patients admitted to the participating institutions will be evaluated on the basis of the inclusion criteria by a consultant in rehabilitation medicine involved in treatment within three days of admission to a stroke service. Time lapsed since the stroke occurred should preferably be less than two weeks. If the patient is still unconscious or incapacitated at this time, inclusion may take place as appropriate within the ensuing four weeks. Standard informed consent procedures will be used. Participants will then be randomly allocated to either the intervention or control group, with the computerized (block) randomization scheme including pre-stratification according to two variables: MRC scale of the elbow flexor (dichotomized in score 1 or scores 2–3); and participating hospital. Two sets of opaque, numbered envelopes will be prepared for each site (one each for MRC score 1 and MRC scores 2–3) containing cards indicating the allocated group. When a new patient is registered, a card will be extracted and the relevant occupational therapist informed of the group allocation.

### Intervention and control group

In accordance with Dutch stroke rehabilitation guidelines, the intervention group patients will receive their regular therapy [3] and additional mental practice-based arm function training. This training will be supervised by the rehabilitation team occupational therapist. After baseline measurements are performed, patients will be familiarized with the mental practice-based therapy during the first session. The patient is educated as to basic imagery principles and the importance of regular imagery training in increasing therapy success. During the first week, the patient will be taught how to use the mental practice techniques to improve arm function by the occupational therapist. A training task tailored to the functional level of the individual patients will be selected by the occupational therapist.

Five different mental practice training tasks derived from the Frenchay Activities Index [26] are available, with gradually increasing difficulty. For all tasks, a training DVD will guide the patient. Each DVD is programmed in three steps starting with a relaxation task to focus attention. Performance of all activities is shown from a 1^st ^person perspective (an 'over-the-shoulder' view). In the first step, correct task performance is shown on screen combined with a verbal explanation. Five repetitions are given. In the second step, task performance is repeated on screen but without verbal explanation; patients are asked to mentally practice the movement. If they are able to actually perform (part of) the task, they may do so concurrently with the imagination of the movement. Again, five repetitions are given. In the third step, no guidance during task performance is given except a visual and verbal cue indicating the end of the task performance over five repetitions. Patients already familiar with this task can immediately start on step two.

DVDs are available for every task for right- and left-handers. Patients must practice at least three times a day for ten minutes each session. During the intervention period, functional arm/hand progress will be evaluated by the occupational therapist every two weeks. If functional level improves, a new task will be chosen and the DVD changed. The total intervention lasts six weeks.

Patients in the control group receive therapy as usual. In addition, they will be instructed to practice additional bimanual upper extremity techniques based on conservative neurodevelopmental (NDT) principles [27]. These exercises are a part of the usual training program, and, in clinical practice, have been accepted as conventional therapy. However, recent studies have questioned NDT's additional value in stroke patients [28,29]. The control group patients will receive a booklet explaining all tasks and be instructed to practice for ten minutes at least three times a day. Every two weeks, the home-based training sessions will be evaluated by the team's occupational therapist. Total contact time with the occupational therapist in the intervention and control groups will be equal.

### Data collection

Measurements will be taken upon entry to the study (T0 = baseline) and 6 weeks (T1 = post treatment); 6 months (T2 = short-term follow-up); 9 months (T3 additional cost questionnaire) and 12 months (T4 = long term follow up) after T0. They will be performed by a rater blinded for therapy modality, and administered wherever the patient is at the time. A blinding check will be performed after each of the four measurement sessions.

### Outcome measures

Outcome measures and assessment moments are presented in table 2.

**Table 2 T2:** Outcome domains and assessment instruments and moments

**Domain**	**Assessment instrument**	**Abbr.**	**T0**	**T1**	**T2**	**T3**	**T4**
Medical information	- Brain lesion		X				
	- Type of stroke		X				
	- Co-morbidity		X				
Basic level of functioning	- Barthel score	BI	X		X		X
	- Frenchay Activity Index	FAI	X*	X	X		X
Cognitive functioning	- Cognitive Log	Cog-log	X				
	- Vividness of Movement Imagery Q.	VMIQ	X				
	- Credibility/Expectancy Q.	CEQ	X				
UEF level of impairment	- Brunnstrom-Fugl-Meyer test	FM	X	X	X		X
	- Strength: part of WMFT	WMFT _str_	X	X	X		X
	- Spasticity: Tardieu scale	MTS	X	X	X		X
UEF level of activity	- Wolf Motor Function Test	WMFT	X	X	X		X
	- Frenchay Arm Test	FAT	X	X	X		X
	- Accelerometry	ACC	X	X	X		X
UEF level of participation	- Impact on Participation and Autonomy questionnaire	IPA					X
	- Stroke-Specific Quality of Life	SS-Qol					X
	- EuroQol	EO-6D		X	X		X
Cost	- Cost questionnaire	CQ	X	X	X	X	X
Process evaluation	- Diary		X				

T0 = baseline

UEF = upper extremity functioning

T1 = 10 weeks after T0

T2 = 6 months after T0

T3 = 9 months after T0

T4 = 12 months after T0

* The FAI on T0 retrospectively assesses the pre-morbid activity level

### Demographic and medical variables

The following socio-demographic variables will be recorded: age, sex, living situation and educational level. The medical variables include systematically scored, stroke-related neurological variables: lesion site, stroke type (hemorrhagic or ischemic), paresis level and co-morbidity. In the questionnaire, information on demographical variables is retrieved. Medical variables as presented above are derived from the medical file of the referring consultant in rehabilitation medicine. Patients will be asked for permission to use this information of their medical file in the informed consent procedure.

### Cognitive functioning

The following aspects of cognitive functioning were measured.

#### General level of cognitive functioning

The Cognitive Log (Cog-log) is a 10-item cognitive screening instrument which measures higher neurocognitive processes including orientation, memory, concentration and executive skills [30].

#### Ability to imagine motor acts

To asses participants' ability to imagine motor acts, the Vividness of Movement Imagery Questionnaire (VMIQ) will be used [31]. Individuals are required to rate the vividness of their imagery on a 5-point scale (1 = as perfectly clear and vivid as normal vision, 5 = no image at all – only a vague awareness of thinking about the movement) for 24 different movements from both an external (i.e. watching somebody else) and internal (doing it yourself) perspective. VMIQ scores have been linked to improvements in motor skills [31].

#### Credibility and expectancy of treatment

The Credibility/Expectancy Questionnaire (CEQ), a simple scale for measuring rationale credibility and treatment expectancy in clinical outcome studies will be used. The credibility and expectancy of mental practice and control training is scored by the patient. This questionnaire demonstrated high internal consistency and good test-retest reliability [32].

